## Abstract

**Background:**

Mindfulness meditation has demonstrated modest benefits for mental health and well-being, although the relationship between practice dose and outcomes is unclear. Meta-analyses and randomized controlled trials have shown mixed results so far, although such results may stem from methodological issues rather than reflecting the absence of an underlying effect. Research outside structured programs suggests that long-term practice time is linked to positive outcomes, but bias due to self-selection over time may explain these results.

**Objective:**

The proposed trial aims to test dose-response effects for an online mindfulness meditation course, examining outcomes and participant engagement across different practice doses. In this pragmatic randomized controlled trial, we hypothesize that larger doses of mindfulness training will yield significantly larger effects and different doses will be significantly associated with variation in participant engagement, with lower engagement evident for higher doses.

**Methods:**

At least 688 healthy adults aged between 18 and 65 years will be randomized to join one of three 4-week online mindfulness courses with daily practices of varying lengths (ie, 10, 20, or 30 min) against a minimally active control condition (4 min). Psychological well-being will be measured using the Warwick-Edinburgh Mental Wellbeing Scale at the baseline, midintervention, and postintervention time points and at 1-month follow-up. Secondary outcomes are psychological distress, anxiety, depression, social anxiety, nonattachment, trait mindfulness, decentering, equanimity, repetitive negative thoughts, emotion regulation, attention control, and emotional reactivity. Other outcomes will be collected weekly and daily during the intervention period. The primary analysis will be undertaken following the intention-to-treat approach. We will also conduct per-protocol secondary analyses on all outcomes (ie, primary and secondary). In addition, we will systematically monitor for possible adverse experiences.

**Results:**

This study began screening and recruitment in May 2024. Recruitment was paused approximately 6 weeks later after a substantial number of participants were identified as being fraudulent and not meeting the eligibility criteria. Recruitment reopened in October 2024, and by the end of 2024, a total of 70 eligible participants were enrolled. Recruitment recommenced in early 2025 and will continue until the end of March 2025 or until the target sample is reached. We estimate that the results will be published by March 2026.

**Conclusions:**

This study will contribute to the evidence base for mindfulness meditation and the question of how much practice people need to engage in to improve well-being and other psychological outcomes.

**International Registered Report Identifier (IRRID):**

DERR1-10.2196/72786

## Introduction

### Background and Rationale

There is now reasonable evidence that mindfulness meditation can have modest beneficial effects on mental health and well-being [1-4]. For an individual starting to practice mindfulness meditation with the objective of improving their mental health and well-being, a natural question is how much practice is needed to achieve certain benefits. The empirical evidence that can be brought to bear on this question is still in its infancy. While benefits have been demonstrated at various practice intensities, there is little evidence of how different doses of daily practice relate to outcomes and whether and to what degree more practice is likely to deliver greater outcomes. Of the 4 empirical studies that have experimentally manipulated session duration to assess dose-response effects for mental health and well-being outcomes, most have failed to detect dose-response effects. However, the authors noted limited dose variation and program duration as limitations, with each of the studies including only 2 dose conditions ranging from 5 to 30 minutes in programs lasting up to 2 weeks of daily practice [5-8]. Meta-analyses investigating dose-response effects in which dose has been defined by the daily home practice component of mindfulness-based programs (MBPs) have so far shown mixed results. A meta-analysis by Parsons et al [9] found a small correlation between self-reported home practice and psychological conditions such as anxiety, depression, and stress (*r*=0.26, 95% CI 0.19-0.34), but a more recent meta-regression from Strohmaier [10] found no statistically significant dose-response effects for the same psychological conditions (where dose was defined as both recommended and self-reported home practice). However, as argued in the study by Bowles et al [11], the absence of evidence for daily practice dose-response effects may not constitute evidence of their absence and may, instead, be due to methodological issues. For instance, as daily practice dosages have not been experimentally manipulated in randomized designs [10], causation about the effects of different dosages cannot be inferred. In addition, as described in the study by Bowles et al [11], given that such meta-analyses were conducted on effect sizes that relate to overall program content, which features multiple active and mutually reinforcing elements [12], it is not known to what extent variation in daily practice time contributes to overall outcomes. Therefore, these dose-response meta-regression models may lack the sensitivity to detect the effects of marginal differences in daily home practice dose and, thus, may be ill-equipped to inform the question of the optimal amount of practice.

Outside the context of MBPs, regular mindfulness meditation dose-response investigations have focused primarily on the relationship between cumulative practice time over the course of an intervention and outcomes. In experimental conditions, such variation in practice time has arisen from natural differences across participants rather than systematic manipulations. While most [13-15], though not all [16], studies support a positive association between time spent practicing and outcomes, such findings may be subject to bias due to the nonrandom distribution of participants across different practice doses. In low-dose settings, while benefits have been demonstrated from single short sessions approximating 15 minutes [17], the measures used in such studies have tended to focus on transient or *state* effects that are more sensitive to change. Therefore, it is not clear what minimum dose is required for efficacious practice when measures focus on trait effects related to the psychological domains that most often motivate practice [18]. In addition, while it is likely that participants in high-dose settings such as meditation retreats represent individuals who derived enduring benefits from the practice, as evidenced by exceptional traits in several psychological and cognitive domains [19], such results may be biased by self-selection [20]. Therefore, there is a lack of empirical work in which practice doses are systematically varied in such a way as to enable differential effects to be causally linked to different practice doses. Moreover, because of this, there is a concomitant lack of empirical evidence of the merits of different practice doses given an individual’s circumstances and disposition and knowledge of the trade-offs from recommending higher and lower doses.

### Objectives

The proposed trial aims to (1) test for a dose-response effect on well-being across the active conditions (which feature different doses of mindfulness meditation instructions and practices; 10, 20, and 30 min) and a minimally active control condition (ie, minimal dose <10 min, <20 min, and <30 min) and (2) explore whether differential rates of program engagement and retention are evident across the 4 (active and control) conditions.

Our hypotheses are that (1) larger doses of mindfulness training will yield significantly larger effects on well-being and (2) different doses will be significantly associated with variation in participant engagement, with lower engagement evident for higher doses.

## Methods

### Trial Design

#### Overview

This study will compare the efficacy of receiving different “doses” of mindfulness training over a 28-day period in a prospective 4-arm, parallel-group randomized controlled trial. Participants will be randomized into 1 of the 4 groups: 10 minutes of meditation per day, 20 minutes of meditation per day, 30 minutes of meditation per day, or a minimal dose of 4 minutes of meditation per day (Figure 1). All participants will be encouraged not to complete any further mindfulness training or practice during the intervention period apart from informal practice during daily life. We chose these session lengths for our dose conditions to align with the range of dose variations that have been used in previous experimental research [5-8], as well as our own review of expert meditation teachers, as outlined by Bowles et al [11].

Self-reported biopsychosocial measures will be evaluated at 4 time points: before randomization (baseline; T0), 2 weeks after randomization (midintervention time point; T0.5), 4 weeks after randomization (postintervention time point; T1), and 8 weeks after randomization (follow-up; T2). In addition, weekly outcomes will be evaluated between T0 and T1. Individual adherence and meditation-related experiences (including adverse events) will be monitored and compared across treatments. The trial will consist of 3 main phases: the run-in period, the intervention period, and the follow-up period, as described in the following sections.

**Figure 1 figure1:**
[figure not shown]
CONSORT (Consolidated Standards of Reporting Trials) flow diagram.

#### Run-In Period

We will randomize after the completion of a 7-day run-in period. Estimates of mindfulness and meditation app user retention over 28 days indicate that most attrition (approximately 90%) occurs within the first 7 days of app installation [21]. Therefore, the run-in period will be used to select the participants most likely to complete study measures. During the run-in period, we will ask participants to complete daily measures (refer to the Outcomes section) as well as listen to four short (5 min) “preparation for meditation” audios covering the following topics: (1) background of the teacher and mindfulness, (2) introduction to the concept of mindfulness, (3) introduction to mindfulness practice, and (4) results from practicing mindfulness. All this content will be accessed via a series of Qualtrics surveys (Qualtrics International Inc) that will be emailed to participants daily. Participants will also be asked to respond to measures that cover personality, sleep, and motivations and expectations. Participants will have successfully completed the run-in period if they engage with ≥57% (ie, at least 4 of the 7 days) of the run-in content.

We will monitor participant response patterns during the run-in period. If such monitoring raises suspicions about the accuracy of the information provided in the prescreening survey (ie, related to the eligibility criteria—most notably, participant identity and country of residence), additional verification procedures may be required. Participants flagged as suspicious who fail to complete or successfully pass additional verification procedures (refer to the Eligibility Criteria section) will be excluded from the study.

#### Intervention Period

Participants who successfully complete the run-in period will be first asked to complete outcome measures at T0 (baseline) via Qualtrics. After completing outcome measures, participants will be randomized to 1 of the 4 study groups and provided with a unique participant identification code along with instructions on how to access the intervention materials. Participants will be asked to use only the specific mindfulness instructions provided for 28 days and complete all survey items when prompted. Throughout the 28-day period and at the conclusion of the intervention, participants will be prompted to complete outcome measures as specified in the Outcomes section.

#### Follow-Up Period

At the conclusion of the 28-day intervention period, participants will be offered full access to any of the 3 higher-dose courses that they choose. At the conclusion of the follow-up period (1 month after completion of the intervention), participants will again complete outcome measures as specified in the Outcomes section and Figure 1.

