Practices will be provided for 6 days each week (ie, a total of 24 guided practices), with participants given the option to practice without guidance on the seventh day. Each variant will teach the same core content; however, the longer variants will have more time to elaborate on this content through teaching and gain experience practicing the guided techniques.

Practice instructions will consist of a brief explanation of relevant theory as well as a set of instructions for the practice in the first few minutes, followed by intermittent guided instructions throughout the duration of the practice. The programs will consist entirely of prerecorded material and will be delivered asynchronously. Therefore, there will be no direct contact between teachers and participants for the duration of the program. While this element constitutes a point of departure from how most MBPs are delivered, Crane et al [30] note that the exact method of delivery is flexible and can vary across MBPs [31].

After the 28-day intervention period, participants will be offered full access to any of the 3 higher-dose courses that they choose. During this time, participants will be free to choose to engage as much or as little with the guided practices as they wish.

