#### Weekly Measures

During the intervention period, additional measures will be obtained weekly (ie, 7, 14, 21, and 28 days after the baseline survey).

*Mindfulness* practice will be assessed using the following items: (1) “In the past week, how many daily sessions of this study’s meditation program did you complete?” (response options: 0-7); (2) “In the past week, on the days you meditated with the study program, approximately how many minutes (on average) was each meditation session?”; (3) “In the past week, how many additional days did you practice meditation?” (response options: 0-7) and “In the past week, on the days you meditated in addition to the study program, approximately how many minutes (on average) was each meditation session?”; (4) “On the days you practised meditation, how many minutes per session did you practice? (this includes the guided sessions in the meditation program)” (response options: 0 to ≥60 min); and (5) “In the past week, how often did you engage in informal mindfulness practice? i.e. mindfully washing dishes, showering, walking etc.” (response options: none of the time to all of the time).

*Adverse events* will be assessed using a modified short form of the Meditation-Related Adverse Effects Scale [50].

*Sleep* will be assessed using a single item from the Sleep Quality Scale [33]: “During the past week, how would you rate your sleep quality overall?” (response options: *terrible*=1, *poor*=2-4, *fair*=5-7, good=7-9, and *excellent*=10).

*Expectancy* will be assessed using the following item: “How effective do you think your training so far has been for your [goal or motivation free-text field from run-in survey]?” (response options: not at all effective to very effective).

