### Assignment of Interventions: Allocation and Blinding

After meeting the selection criteria and completing the run-in period and baseline measures, participants will be randomized to 1 of the 4 groups. Participants will be blinded to the dosing nature of the study and will only be told that they are participating in a trial to test the effects of a 28-day mindfulness meditation intervention. While participants will be informed of their group allocation (eg, group 1), they will not be informed of what the number refers to.

Randomization will be remote and computer based. The allocation process will be automatically concealed, so researchers will not be able to predict or influence who will be randomized to which group. Members of the research team will not be informed of participants’ allocation until after final analyses have been completed, and analyses will be conducted blind to group allocation.

Group allocation will be based on block randomization, with an equal number of participants allocated to each condition for every 24 participants. The randomization process consists of prepopulating a list of randomized allocated group orderings and putting this list in an Amazon Web Services Simple Queue Service First-In-First-Out queue (condition queue), from which group allocation occurs by polling an item from the queue. It is necessary to rebuild this condition queue regularly as queues have a maximum life span of 14 days. We decided to rebuild every night (as opposed to every 14 days), although the rebuilding process maintains the current allocated group orderings from the queue it replaces.

To generate the group ordering (condition list) that is placed on the condition queue, the following steps are taken using a Python script (Python Software Foundation) with the random seed set to 2023: (1) a list with 24 items constituting 1 block is created containing 6 occurrences for each group (ie, 1, 2, 3, 4, 1, 2, 3, 4...1, 2, 3, 4), (2) we randomize this list and then add it to the condition list, (3) this process is repeated 72 times to create a condition list of length 1728 (ie, 72 blocks of 24), and (4) this condition list is uploaded to the condition queue.

This method equates to block randomization as, for every 24 assignments to the condition list, an equal number of participants (ie, 6) will be randomly assigned to each group.

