#### Effectiveness Analyses

A constrained longitudinal data analysis method [57] will be used to build the linear mixed-effects model estimating the effect of the interventions on the primary outcome. The model will incorporate study visit (T0 and T1) as a categorical variable, intervention (10, 20, and 30 min each vs the minimal dose), and intervention by study visit interaction as main effects. The model will assume a common baseline mean of the outcome across the 4 intervention groups and an unstructured variance-covariance among the repeated measurements.

Models analyzing secondary outcomes will incorporate study visit (T0, T0.5, and T1) and intervention (10, 20, and 30 min each vs the minimal dose) as categorical variables. Secondary continuous outcomes will be analyzed similarly to the primary outcome (ie, the constrained longitudinal data analysis described previously). Additional analyses will include follow-up assessments (ie, T2) in the model.

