Given our focus on the question of dose-response effects, our analysis examines the effectiveness of different doses relative to each other (and to a minimally active control). Therefore, we cannot make inferences about the effectiveness of the intervention relative to other psychosocial interventions. However, the intervention shares several characteristics that align with the definition of MBPs by Crane et al [30]. Therefore, we are relying on this evidence base, which has demonstrated the effectiveness of similar MBPs, while focusing on one aspect of such programs that is less empirically validated, namely, whether and to what degree shorter or longer daily practices are more beneficial.

All outcome data are self-reported, introducing the potential for recall bias, social desirability bias, and inaccuracies. Despite these limitations, self-report measures were chosen for their practicality and suitability for collecting data online for well-being, the primary outcome, and various secondary outcomes.

Finally, we are tracking and will follow up on reports of adverse experiences throughout the intervention and follow-up periods. Britton [67] has hypothesized that meditation-related adverse experiences and problems with sleep may be more likely to occur at higher doses. While our dosage may still be relatively low compared to that of high-dose settings such as residential retreats, our study design will allow us to explore the question of whether and when higher doses of mindfulness may be riskier than lower doses.

Considering these strengths and limitations, our study will make a significant contribution to the growing literature on the dose-response effects of mindfulness meditation, providing much-needed empirical support to the question of whether and when larger doses are more beneficial than smaller ones. These findings may inform practical guidelines, helping beginner meditators and their advisors—whether in health, well-being, or spiritual contexts—estimate the amount of practice required to achieve particular outcomes.

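### All arms are offered every higher-dose course from day 28, so the T2 contrast estimates assigned dose followed by open access, not durability of the randomized dose

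*Protocol article*

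**What the plan says.** **Access.** Follow-Up Period makes the offer: "At the conclusion of the 28-day intervention period, participants will be offered full access to any of the 3 higher-dose courses that they choose". The Interventions section repeats the offer and adds that "participants will be free to choose to engage as much or as little with the guided practices as they wish".

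**End of the restriction.** Intervention Period: "Participants will be asked to use only the specific mindfulness instructions provided for 28 days". Nothing restricts practice after that.

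**Timing of follow-up.** Trial Design, Overview, places the last assessment at "8 weeks after randomization (follow-up; T2"). T1 is at 4 weeks.

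**Analysis.** Effectiveness Analyses: "Additional analyses will include follow-up assessments (ie, T2) in the model". Efficacy Analyses does the same for the per-protocol model. In both, the factor is randomized arm.

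**Practice data.** Weekly Measures: "During the intervention period, additional measures will be obtained weekly (ie, 7, 14, 21, and 28 days after the baseline survey"). The Figure 2 legend places the daily momentary measures between T0 and T1. None of the T2 measures listed under Outcomes asks which course was used or how long the participant practised.

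**Blinding.** Allocation and Blinding: "Participants will be blinded to the dosing nature of the study".

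**Harms.** Strengths and Limitations: "we are tracking and will follow up on reports of adverse experiences throughout the intervention and follow-up periods", with the aim of exploring whether higher doses carry more risk. That section does not mention the open access.

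**The concern.** T2 is the only assessment after the prescribed practice ends, so readers will look to it for evidence that a dose effect lasts. Before it come four weeks in which any participant may take up any of the three longer courses. A null T2 contrast could mean that the effect faded, or that low-dose participants caught up by moving to a longer course. A persisting contrast could mean a lasting effect, or that the high-dose arms kept practising more. Without data on post-T1 practice these cannot be told apart.

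The same applies to harms: an adverse experience in weeks 5 to 8 cannot be attributed to the assigned session length if the participant has since chosen another.

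There is also a smaller point on sequence. The T1 survey and the offer both fall at the conclusion of the 28 days. A participant who saw a choice of courses before answering T1 might guess that dose is under study, and T1 carries a self-reported primary outcome.

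**Working it through.** **1. Timeline.** Access opens at week 4 and T2 is at week 8, so 8 − 4 = 4 weeks of open access precede T2. The well-being scale asks about the previous 2 weeks, so its T2 window is weeks 7 to 8, wholly inside open access.

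**2. What the T2 contrast estimates.** For a higher-dose arm H and a lower-dose arm L, let D be the difference that would exist at T2 without later course use, and g_H and g_L the mean effects of course use after day 28. Then:

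T2 contrast = D + (g_H − g_L)

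Randomization makes the left side a valid comparison of assignments. The plan describes nothing that identifies the bracket. Taking D = 1.97 (the planned difference) for illustration:

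- g_L = 0.985, g_H = 0 gives 1.97 − 0.985 = 0.985.
- g_L = 0, g_H = 0.985 gives 1.97 + 0.985 = 2.955.

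So the direction is not determined. Shrinkage is plausible if mainly low-dose participants move up, but uptake may differ by arm either way.

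**3. The plan's own sample size.** Inputs from Sample Size: difference 1.97, SD 9.84, correlation 0.83, two-sided significance level 0.02, power 80%.

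- Change-score SD = 9.84 × √(2 × (1 − 0.83)) = 9.84 × √0.34 = 5.74.
- n per arm = 2 × 5.74² × (2.326 + 0.842)² / 1.97² ≈ 170.3, rounded up to 171. Total 4 × 171 = 684, against 688 stated (172 per arm).
- 688 / 0.80 = 860, as stated.

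The stated figures reproduce closely. They concern T1 and are not affected by this point.

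**4. Illustration at T2.** Assumptions: 172 per arm, the same variance and the same 0.02 level. The difference shrinks by an assumed fraction s, which the documents do not give.

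SE = 5.74 × √(2/172) ≈ 0.619; power = Φ(1.97 × (1 − s)/0.619 − 2.326)

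| s | difference | power |
|---|---|---|
| 0 | 1.97 | 0.804 |
| 10% | 1.77 | 0.705 |
| 25% | 1.48 | 0.525 |
| 50% | 0.99 | 0.231 |
| 75% | 0.49 | 0.063 |

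The fraction s equals the share of the lower arm taking up a longer course only if each of them gains the full effect within four weeks and the other arm does not change.

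**5. Per-protocol model.** A complier is someone reporting more than 66.67% and less than 117% of the 24 sessions of the 28-day course. That status is settled by day 28. The named weighting covers prerandomization factors. The planned causal diagram will consider postrandomization confounders too, but those associated with being a complier. None of this covers practice in weeks 5 to 8, so a T2 per-protocol contrast cannot be read as efficacy of a dose under high compliance.

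**The case against.** **Randomization is intact.** A reader might infer that T2 no longer compares the randomized arms. That goes too far. The intention-to-treat contrast still does, and the trial's stated purpose concerns prescribed doses, prescribed for 28 days, in a pragmatic design. What changes is the meaning of the contrast.

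**T2 carries limited weight.** The primary outcome is at T1, the primary model uses T0 and T1 only, and T2 enters as an additional analysis. Neither the objectives nor the hypotheses promise durability. This stands, and it limits the importance of the point.

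**Non-recording is an inference.** A reader might conclude that post-T1 practice is not recorded. The article is condensed, its figures are not shown and platform logs are not discussed. It says adverse experiences are tracked in follow-up although the measure is described only for the intervention weeks, so it evidently does not list everything collected later. The exact statement is that no recording is described.

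**Unblinding at T1 is not shown.** The end-of-intervention survey is described under Intervention Period and the offer under Follow-Up Period, so the natural reading is survey first. The trigger and wording of the offer are not given. What remains is only that the order is not fixed.

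**Deferring the offer is no clean cure.** With recruitment under way, a change of access would mix two T2 conditions across cohorts. Participants could also go on practising by choice after day 28. This stands, and deferral is therefore not the recommendation.

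**Harms.** Weekly adverse-event data from the 28 days at assigned dose remain available for the dose-risk question. This too stands; the caution applies only to follow-up.

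**Conclusion.** The point holds as one of interpretation and data capture at a secondary time point. The T2 intention-to-treat contrast estimates the effect of 28 days at an assigned dose followed by open access to any course. It does not estimate durability of the randomized dose, and the article does not say so. The per-protocol T2 analysis is the weakest part, because neither its complier definition nor its named adjustment reaches past day 28.

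No figure for bias can be given: uptake is not in the documents and either direction is possible. The power range of 0.804 down to 0.063 is illustrative and rests on assumed shrinkage, 172 per arm at T2 and the primary significance level.

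The T1 analysis and the sample size are unaffected, on the condition that no participant receives the offer before answering T1.

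**What to change.** 1. State that the offer of courses is sent only after the T1 survey is submitted or its window has closed. This needs at most a change to the trigger of the message.
2. If not already there, add to the T2 survey the existing weekly practice items, reworded for the period since T1, plus a question on which course was used.
3. Define and report T2 efficacy contrasts, and any dose-specific harm in follow-up, as 'after open access to all doses'. This can still be done for participants already past T2.
4. Make no per-protocol efficacy claim at T2 unless the analysis accounts for practice after T1.
5. List the open access among the limitations.

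Whether to defer the offer until after T2 is for the investigators to decide, weighing the mixture of T2 conditions it would create between earlier and later participants.

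Cost: a short amendment, a few extra T2 items and a more limited T2 conclusion. Post-T1 practice would still be missing for those who completed T2 before the items were added.
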